## Abstract

Cognitive impairment, defined as a decline in memory and executive function, is one of the most severe complications of traumatic brain injury (TBI). Patients with TBI are often unable to return to work due to cognitive impairment and their overall quality of life is reduced. TBI can bring a serious economic burden to patient's families and to society. Reported findings on the efficacy of repetitive transcranial magnetic stimulation (rTMS) in improving cognitive impairment following TBI are inconsistent. The purpose of the proposed study is to investigate whether rTMS can improve memory and executive function in patients with TBI. Herein, we propose a prospective randomized placebo-controlled (rTMS, sham rTMS, cognitive training), parallel-group, single-center trial. 36 participants with a TBI occurring at least 6 months prior will be recruited from an inpatient rehabilitation center. Participants will be randomly assigned to the real rTMS, sham rTMS, or cognitive training groups with a ratio of 1:1:1. A 20-session transcranial magnetic stimulation protocol will be applied to the left and right dorsolateral prefrontal cortices (DLPFC) at frequencies of 10 Hz and 1 Hz, respectively. Neuropsychological assessments will be performed at four time points: baseline, after the 10th rTMS session, after the 20th rTMS session, and 30 days post-intervention. The primary outcome is change in executive function assessed using the Shape Trail Test (STT). The secondary outcome measures are measures from neuropsychological tests: the Hopkins Verbal Learning Test (HVLT), the Brief Visuospatial Memory Test (BVMT), the Digit Span Test (DST). We report on positive preliminary results in terms of improving memory and executive function as well as beneficial changes in brain connectivity among TBI patients undergoing rTMS and hypothesize that we will obtain similar results in the proposed study.

## Introduction

The Centers for Disease Control and Prevention (CDC) defines a traumatic brain injury (TBI) as a mechanical injury to the brain caused by a collision, blow, or bump (1). TBI is a major health problem worldwide owing to the complex complications and sequelae associated with this condition. TBI affects more than 50 million people worldwide each year, including approximately 1.7 million people in the United States alone (2, 3). Although effective treatment in the acute phase has greatly improved survival among TBI patients, an estimated 5–7 million TBI patients in Europe and the United States suffer from multiple complications.

Cognitive impairment is the main clinical symptom of TBI. Cognitive impairment following TBI is often characterized by attention deficits, memory loss, and decreased executive ability. TBI can initiate a long-term neurodegenerative process that leads to pathological features similar to those of Alzheimer's disease (AD) (4–6). More than 50% of TBI patients experienced an impaired state of consciousness (i.e., a coma or a vegetative state), which has reported to persist in the form of long-term cognitive impairment (7). It is well known that deficits in executive function and memory are commonly detected within TBI, and these deficits are more difficult to treat as compared with deficits associated with other cognitive disorders as a result of the vulnerability of the affected brain regions (such as the frontal and temporal lobes). These sequalae negatively affect patients' quality of life as well as their rehabilitation process (8). Numerous studies have demonstrated that cognitive training can improve multiple cognitive domains inTBI involving reasoning, goal management, attention, as well as reorganized modular networks (9–11).

Recently, repetitive transcranial magnetic stimulation (rTMS), a neuromodulatory tool, can induce neural activity and efficiently improve cognitive function (12–15). A large number of existing studies confirm that repetitive transcranial magnetic stimulation (rTMS) of the dorsolateral prefrontal cortices (DLPFC) may strengthen the connections within the brain network, which may increase the strength of the interconnections between the cortex and hippocampus, resulting in cognitive enhancement (16, 17). High frequency (≥ 5) rTMS (HF-rTMS) is the most widely used technique to improve cognitive function in clinical trials as well as in healthy individuals (18). In a review of cognitive enhancemen using rTMS, 10 Hz was found to be the frequency used in most studies (19). Most studies found that HF-rTMS on left DLPFC improved memory and processing skills in healthy, depressed, posttraumatic stress disorder (PTSD), schizophrenic, AD, and mild cognitive impairment (MCI) populations. However, some showed no significant effect. In another review of the efficacy of LF-rTMS on cognition, the findings of 1 Hz rTMS on the right DLPFC on improving cognitive function in mood disorders, psychosis, stroke and other organic disorders were also inconsistent (20).

A Systematic Review Also Reported That RTMS Enhances Neuroprotection and Recovery Following TBI in Animals (21). However, There Have Been Fewer Studies Investigating the Effects of RTMS on Cognitive Function in Humans Presenting With TBI, and Most Investigations to Date Have Been Clinical Case Reports or Case Series. To the Best of Our Knowledge, Only two RCTs Have Been Reported to Dates Neville et al. Reported That Stimulating the Left DLPFC With 10 Hz RTMS Did not Improve Cognitive Function in Subjects, While Lee and Kim Stimulated the Right DLPFC With 1 Hz RTMS, Which Improved Cognitive Function in Subjects (22, 23). They Reported the Safety and Efficacy of Implementing RTMS on Bilateral DLPFC and may be an Alternative Type of Intervention to Improve Cognitive Function. Also, Some Studies Suggested That at Least 4 Weeks of RTMS Intervention may be Necessary to Improve Cognitive Function.

Therefore, the proposed study aims to examine HF and LF, bilateral rTMS for the cognitive dysfunction in patients with TBI. In addition, magnetic resonance imaging (MRI) will be utilized to explore the association between brain structure and functional connectivity, as well as the cognitive effects of rTMS. The preliminary hypotheses of our study are (1) 4 weeks of bilateral high- and low-frequency rTMS is more effective in improving cognitive function in patients with TBI than sham stimulation and cognitive training and (2) structure MRI markers and functional connectivity pre- and post-intervention will be observed.

## Materials and Methods

### Study Design

The study is a prospective randomized placebo controlled, parallel-group trial that will be conducted at the Affiliated Hospital and the Second Clinical Medical College of North Sichuan Medical University. The protocol has been registered with the China Clinical Trial Registry (item number: ChiCTR2100050753). Our study will show improvement in cognitive function in patients with TBI following rTMS bilateral DLPFC intervention. The findings may provide a rationale for an approach of rTMS intervention for cognitive function in patients with TBI. Thirty-six patients with TBI will be enrolled in the trial. The physicians will provide patients with detailed information about the trial in verbal and written form before the trial begins.All patients will voluntarily sign an informed consent form. All patients will be screened according to eligibility criteria. 36 subjects will be randomized in a 1:1:1 ratio into the real-rTMS group, the Cognitive training group and the sham-rTMS group. All subjects will be required to perform neuropsychological assessments at before intervention, post-10 sessions, post-20 sessions, and 30 days after the intervention. MRI will be performed at pre-intervention and post-20 sessions. All patients will receive intervention for 4 weeks (30 minutes per day, 5 days per week). The diagram and schedule for the study are shown in Figure 1 and Table 1.

**Figure 1 F1:**
[figure not shown]
Flowchart of the study design. rTMS, Repetitive Transcranial Magnetic Stimulation; fMRI, functional Magnetic Resonance Imaging.

**Table 1 T1:** Schedule of enrollment, assessment, and interventions.

			**Screening**	**Randomization**	**Treatment**				**Follow up**
					**10 sessions**		**20 sessions**		
	**Timepoint**		**Within two weeks**	**Day 0**	**Week 1**	**Week 2**	**Week 3**	**Week 4**	**Post-30 day**
				**T1**	**T2**		**T3**		**T4**
Enrollment
	Informed consent		√						
	Demographic information		√						
	Medical history		√						
	Eligibility assessment		√						
	Radom allocation			√					
Interventions	Real rTMS				√	√	√	√	
	Sham rTMS				√	√	√	√	
	Cognitive training				√	√	√	√	
Assessment	Screening outcome
	Awareness status	RLAS	√					
	Intellectual functioning	MoCA	√					
	Primary outcome			√	√		√		√
	Executive function	STT, DST					
	Secondary outcomes			√	√		√		√
	Memory	HVLT, BVMT					
	Brain connectivity	fMRI			√			√	

*RLAS, Rancho Los Amigos Scale; DST, Digit Span Test; MoCA, The Montreal Cognitive Assessment; rTMS, repetitive transcranial magnetic stimulation; STT, The Shape Trail Test; HVLT, Hopkins Verbal Learning Test; BVMT, Brief Visuospatial Memory Test; fMRI, functional Magnetic Resonance Imaging*.

### Ethical Approval and Consent to Participate

The study has been approved by the Ethics Committee of Nanchong Central Hospital. All participants will provide written informed consent forms at the time of recruitment. Moreover, all study procedures will be conducted in accordance with the principles of the Declaration of Helsinki in its later amendments. Written informed consent will be provided by the participants or their legal guardians.

### Sample and Recruitment

TBI patients will be recruited through inpatient units at the Affiliated Hospital and the Second Clinical Medical College of North Sichuan Medical University. Recruited participants will be required to present with a clear diagnosis of TBI according to U.S. Centers for Disease Control and Prevention (CDC) guidelines based on clinical and imaging findings. The informed consent process will be carried out by the Principal Investigator. Once participants agree to sign the informed consent form, they will be screened to confirm that they are eligible for study participation according to the following inclusion criteria.

### Inclusion Criteria

(a) Adult patients older than 18 and younger than 60 years.(b) Rancho Los Amigos Scale of Cognitive Functioning (RLAS) score categorizations >VI.(c) Montreal Cognitive Assessment (MoCA) scores <26.(d) Diagnosis of TBI occurring ≥ 6 months prior.(e) patient is right-handed.

### Exclusion Criteria

(a) History of mental or psychological illness.(b) An implanted device or metal in the brain or body.(c) Skull defect.(d) History of epilepsy.(e) Cardiac pacemaker or cochlear implant.

### Sample Size Estimation

Sample size calculations were based on non-inferiority tests, as the purpose of this study was to show that the rTMS intervention was not inferior to cognitive training. According to studies showing that the effect size of working memory training on MCI is 0.74 and executive function is 0.575, we calculated the sample size using PASS 15 (effect size is 0.7, α is 0.05, power is 0.9). sample sizes of *n* = 10, *n* = 10, and *n* = 10 are obtained for the three groups. Moreover, two additional patients will be added to each group to compensate for possible dropouts. A total of 12 patients will be allocated to each group.

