### Outcome Measures

The primary outcome of the proposed study is current executive functioning as measured by the Shape Trail Test (STT), which was revised for the Chinese-speaking population based on the Trail Making Test (TMT). The secondary outcome measures are neuropsychological test findings based on the Hopkins Verbal Learning Test (HVLT), the Brief Visuospatial Memory Test (BVMT), and the Digit Span Test (DST), as well as evaluations of the safety and tolerability of rTMS in patients with TBI.

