### Statistical Analysis

Baseline comparisons were used to examine potential differences between real-rTMS, sham-rTMS, and cognitive training, which ensured that there are no differences between the three groups. Potential baseline differences between the three groups will be detected. Gender, education, and pathological characteristics (axonal injury or cerebral hemorrhage) will be measured using Chi-square tests. The One-way ANOVA is conducted to analyze the outcome and information of the pre-intervention assessment. The Kolmogorov-Smirnov test will be used to evaluate the normality of distributions. If a normal distribution is confirmed, data will be presented as means and standard deviations (SD) and ANOVA will be used to analyze the effects at T1, T2, T3, and T4, with Bonferroni correction for multiple comparisons as a *post hoc* test. if it does not conform to a normal distribution, it will be tested using Kruskal-Wallis (non-parametric test). *P*-values <0.05 will be considered statistically significant. Data will be analyzed using the Statistical Package for Social Sciences (SPSS) software (v.22.0; SPSS, Inc., Chicago, IL, USA). MRI data will be examined in statistical parametric mapping using independent Student's *t*-tests. The statistical significance is P <0.001. To find other correlated factors that may have an impact on the efficacy of the intervention, correlations between changes in MRI data and changes in behavioral data will be calculated. Only patients completing the rTMS protocol will be included in analyses.

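### The sample size rests on non-inferiority to cognitive training, the hypothesis is superiority and the analysis tests only for a difference; the stated n does not follow from a non-inferiority calculation on the stated inputs

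*Protocol article*

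**What the plan says.** Three sections of the Protocol article bear on the comparison of rTMS with cognitive training.

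- **Sample Size Estimation.** "Sample size calculations were based on non-inferiority tests", because "the purpose of this study was to show that the rTMS intervention was not inferior to cognitive training". The inputs are that "the effect size of working memory training on MCI is 0.74 and executive function is 0.575", followed by "we calculated the sample size using PASS 15" with "effect size is 0.7, α is 0.05, power is 0.9". The result is 10 per group in each of the three groups, raised to 12 for dropout.
- **Introduction.** The first hypothesis is that four weeks of bilateral rTMS "is more effective in improving cognitive function in patients with TBI than sham stimulation and cognitive training".
- **Statistical Analysis.** If the data are normal, "ANOVA will be used to analyze the effects at T1, T2, T3, and T4", with Bonferroni-corrected post hoc comparisons; otherwise Kruskal-Wallis is used. Significance is P<0.05. Only completers of the rTMS protocol are analysed.

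The primary outcome is the Shape Trail Test (STT), a completion time where shorter is better. The article gives no standard deviation for it.

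**The concern.** For the same pair of arms, one section aims to show that rTMS is not worse than training and another that it is better. The planned tests ask a third question, whether the groups differ at all. Failing to reject equality is not evidence of non-inferiority, which requires a confidence bound to be compared with a margin. The inputs to the sample size calculation include no figure described as a margin, although a non-inferiority sample size cannot be computed without one.

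At stake is what the trial may claim. Significant superiority over training would settle both objectives. Any other result would leave the purpose used to justify the sample size unanswered, with nothing in the analysis section to say so. If the stated n came from a different kind of calculation, the stated 90% power also does not belong to the stated purpose.

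**Working it through.** **Inputs.** Effect size 0.7 (type of index not stated), α 0.05 (sidedness not stated), power 0.9, three groups, 10 per group before dropout and 12 after: all from Sample Size Estimation. SD = 1 is an assumption, so differences are in SD units.

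**1. Reproducing the stated n.** For a one-way ANOVA with k = 3 and n per group, power is P[F′(k−1, 3n−3, λ) > F(0.95; k−1, 3n−3)], where F′ is noncentral F and λ = 3n·f². With f = 0.7:

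| n per group | power |
|---|---|
| 9 | 0.873 |
| 10 | 0.911 |

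The smallest n for 90% power is exactly 10. This is a test of difference, and it requires 0.7 to be Cohen's f. With three groups, f = 0.7 means that the extreme means lie between 0.7 × 3/√2 = 1.48 SD and 0.7 × √6 = 1.71 SD apart. If the cited 0.575 and 0.74 are standardized mean differences, the assumed spread is at least twice as large.

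**2. The named method.** For non-inferiority with margin m and true difference 0, n per group = 2(z₁₋α + z₀.₉)²/m². At m = 0.7:

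- one-sided 0.05: 2(1.645 + 1.282)²/0.49 ≈ 35, or 36 with the noncentral t;
- one-sided 0.025: 2(1.960 + 1.282)²/0.49 ≈ 43, or 44 with the noncentral t.

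A superiority test of a pairwise difference of 0.7 SD gives the same numbers (36 one-sided, 44 two-sided). With 12 per group the power is 51% at one-sided 0.05, and 37% at one-sided 0.025 or two-sided 0.05. With 10 it is 44% and 32%.

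**3. What 12 per group can exclude.** For one pairwise contrast the distance from estimate to confidence bound is t·√(2/n).

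| | one-sided 0.05 | two-sided 95% |
|---|---|---|
| n = 12 (22 df) | 1.717 × 0.408 = 0.70 SD | 2.074 × 0.408 = 0.85 SD |
| n = 10 (18 df) | 1.734 × 0.447 = 0.78 SD | 2.101 × 0.447 = 0.94 SD |

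Even an observed difference of exactly zero therefore excludes only margins above 0.70 to 0.85 SD with 12 per group. The cited training effects are 0.575 and 0.74.

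**4. What a non-significant test would mean.** With 12 per group, if rTMS were truly 0.7 SD worse than training, a two-sided t test at 0.05 would be non-significant 62.5% of the time, and 78.5% with Bonferroni over three pairs. If it were truly 0.5 SD worse, the unadjusted figure is 78%. These scenarios are illustrative; they show that non-significance carries little information about inferiority.

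**The case against.** Several points on the other side have force.

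- **Missing detail may sit elsewhere.** A margin or a confidence-interval rule could be in a full protocol or analysis plan. That is right, so the absent margin carries no weight alone. What remains is that the article itself states a purpose, a hypothesis and a test that do not agree.
- **The purpose is not wholly unanswerable.** A significant rTMS advantage over training in the planned post hoc comparison would imply non-inferiority. The problem is confined to every other result.
- **A non-inferiority formula can give about 10.** A true rTMS advantage of 0.7 SD plus a margin of 0.6 to 0.8 SD yields 8 to 11 per group at one-sided 0.05 and 10 to 13 at one-sided 0.025. The article states neither such a margin nor that 0.7 is an assumed advantage over training.
- **The precision figure depends on sidedness.** At one-sided 0.05 with 12 per group the distance is 0.70 SD, which lies inside the cited range of training effects. It would be wrong to say without qualification that it exceeds them.

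A reader might also infer that a non-significant ANOVA will be reported as non-inferiority, so that a clearly worse rTMS would pass. No section says so; the analysis section says only what counts as significant. It is a risk left open, not a planned rule. A reader might likewise infer that the sham arm played no part in the sizing. That is unsupported: the article reports n for three groups, and the calculation that reproduces 10 includes sham.

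**Conclusion.** The point holds as a contradiction within the article. The purpose and sizing are non-inferiority to training, the hypothesis is superiority over sham and training, and the analysis tests for a difference. Unless rTMS is significantly better than training, the planned analysis cannot establish non-inferiority.

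The sample size statement also disagrees with its own number. Ten per group is what an omnibus ANOVA with f = 0.7 needs; a margin or pairwise difference of 0.7 SD needs roughly three and a half to four and a half times as many (36/10 to 44/10). That the ANOVA was the calculation actually run is an inference from the exact match, not something the article states.

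The sizes rest on SD = 1, a true difference of zero for the non-inferiority figures, two-group t tests, and both readings of the unstated sidedness. Using the pooled three-group error instead changes little (0.69 rather than 0.70 SD at one-sided 0.05). This should be settled before analysis, because the trial's main claim is otherwise undefined.

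**What to change.** Choose one objective for the trial before analysis and align the three sections with it.

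**Simplest course, consistent with the Introduction and the planned tests.**
- Delete the non-inferiority purpose and the non-inferiority label on the sample size.
- Name one superiority contrast on the STT as confirmatory, for example real versus sham rTMS.
- Report rTMS versus training as a difference with a 95% confidence interval, and state that a non-significant difference will not be interpreted as non-inferiority.
- Restate the basis for n and the power delivered for the named contrast: at 0.7 SD, two-sided 0.05, about 37% with 12 per arm and 32% with 10.

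**If non-inferiority is kept.** State and justify a margin on the STT scale, compare a confidence bound with it at a stated one-sided level, and restate the power that 12 per arm gives. At an assumed margin of 0.7 SD and true difference 0 this is 51% (one-sided 0.05) or 37% (one-sided 0.025).

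**Cost.** If the enrolment target stays at 36, the change is to text, but the article must give up the 90% power statement for the chosen contrast. Restoring 90% for a pairwise 0.7 SD difference at two-sided 0.05 would take 44 per group, or 3 × 44 = 132 evaluable participants across three equal arms.

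### Non-inferiority to cognitive training is the stated purpose, but it conflicts with the stated hypothesis and does not depend on either treatment beating the randomised sham arm

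*Protocol article*

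**What the plan says.** All references are to the protocol article.

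- **Sample Size Estimation.** "Sample size calculations were based on non-inferiority tests", because "the purpose of this study was to show that the rTMS intervention was not inferior to cognitive training". The planning effects are that "the effect size of working memory training on MCI is 0.74 and executive function is 0.575", and the inputs are "effect size is 0.7, α is 0.05, power is 0.9". No margin is given. Sham appears only as one of the three equally sized groups.
- **Introduction, last paragraph.** Hypothesis (1) is that four weeks of bilateral rTMS improves cognition more than sham and more than cognitive training. That is superiority over both.
- **Study Design.** The trial is described as placebo controlled, and "36 subjects will be randomized in a 1:1:1 ratio into the real-rTMS group, the Cognitive training group and the sham-rTMS group".
- **Statistical Analysis.** Groups are compared by ANOVA with Bonferroni post hoc tests, or by Kruskal-Wallis if the data are not normal. There is no non-inferiority test, no confidence-interval rule and no order of comparisons.

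**The concern.** Finding rTMS no worse than training shows benefit only if the trial also shows that training, or rTMS itself, does something in these patients. The sham arm could show this, but no statement ties the conclusion to it.

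The article gives reasons to take the no-effect case seriously:

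- The planning effects for training come from MCI. The Introduction cites training studies in TBI but gives no effect size from them.
- The Introduction and Discussion report a randomised trial of 10 Hz left-sided stimulation in brain injury that found no difference from sham on part B of the Trail Making Test. The STT, the primary outcome here, was revised from that test. A second trial, of 1 Hz right-sided stimulation, is reported as positive, so the evidence is mixed.
- The accuracy figures quoted for the STT are for people over 65, while this trial enrols adults under 60. They also describe classification, not response to change.

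At stake is a published conclusion that rTMS is as good as an established therapy, drawn from two treatments of which neither worked.

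**Working it through.** **1. The plan's own figure.** Inputs from Sample Size Estimation: effect size 0.7, α 0.05, power 0.9, 10 per group, 12 after the dropout allowance.

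- One-way ANOVA, three groups, Cohen's f = 0.7. The noncentrality is f² × N = 0.49 × 30 = 14.7, which gives power 0.911 at 10 per group (0.873 at 9). This reproduces n = 10.
- Non-inferiority with margin 0.7 SD and no true difference: n = 2(z₁₋α + z₀.₉)² / 0.7². One-sided 0.05 gives 2(1.645 + 1.282)² / 0.49 ≈ 35 per group. One-sided 0.025 gives 43. Neither reproduces 10.
- A non-inferiority calculation comes near 10 only if rTMS is also assumed truly better than training. For example, a 0.7 SD true advantage on top of a 0.7 SD margin gives 9 or 11. The article states no such assumption.

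**2. Chance of declaring non-inferiority when all three arms are equal.** Assumptions: unit SD, variance pooled over three arms, one-sided 0.05. The margin m is assumed, because none is stated. The test statistic is (rTMS − training + m) / SE, with improvement counted as positive and SE = SD × √(2/n). It has a noncentral t distribution with noncentrality m√(n/2) and 3n − 3 degrees of freedom. For m = 0.7 and n = 10, the noncentrality is 0.7 × √5 = 1.565 and the critical value on 27 df is 1.703, which gives 45%.

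| Margin | 10 per arm | 12 per arm |
|---|---|---|
| 0.35 SD | 19% | 21% |
| 0.5 SD | 29% | 33% |
| 0.7 SD | 45% | 51% |

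Pooling over the two compared arms only changes these by less than one percentage point.

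**3. The same with a sham condition.** If rTMS must first beat sham at two-sided 0.05, the chance of a non-inferiority claim under equal arms cannot exceed 2.5%. By simulation it is about 2% (1.7% to 2.3%) for every cell of the table.

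**4. The price of the condition.** Suppose rTMS and training are both truly 0.7 SD better than sham.

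- rTMS versus sham, two-sided 0.05: power 32–33% with 10 per arm and 37–38% with 12, depending on the pooling.
- Both steps, with a 0.7 SD margin for the second: 23% with 10 per arm and 28% with 12. Without the sham step, the non-inferiority test alone succeeds in 45% and 51%.
- 90% power for rTMS versus sham at d = 0.7 needs 2(1.960 + 1.282)² / 0.49 ≈ 43 per group.

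**The case against.** The strongest reply is that sham is not ignored. The Introduction already hypothesises superiority over sham, the trial is called placebo controlled, and three-group post hoc testing would normally include rTMS versus sham. This is correct. A reader might infer that the sham comparison is absent from the plan, and the document does not support that. What stands is narrower: the comparison is available, but a failed sham comparison would not block a non-inferiority conclusion. The Introduction does not settle the matter, because it also claims superiority over training, which conflicts with Sample Size Estimation. If that conflict were resolved by dropping non-inferiority, this point would fall away.

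Second, the percentages describe a test and a margin that the article does not contain. This is also correct. A reader might take 45% as the trial's actual error rate, or extend the range to 1.0 SD, where the same calculation gives about 70%. Neither is supported. No margin is stated, and 1.0 SD exceeds every effect size in Sample Size Estimation (0.74, 0.575 and 0.7). The figures only illustrate the logic.

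Third, a reader might infer that the comparison with training is uninformative whenever rTMS fails to beat sham. It is not. If training beats sham, the trial has shown that it can detect an effect, and the rTMS versus training interval carries information.

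Fourth, the order of testing is often left to a full protocol or SAP, which is not shown. That would excuse silence on detail. It does not excuse a stated purpose that contradicts the stated hypothesis and has no matching test in the analysis section.

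**Conclusion.** The point holds in a limited form. The article states one purpose (non-inferiority to training), a different hypothesis (superiority to sham and to training) and an analysis that tests only for differences. It does not make a non-inferiority conclusion depend on a demonstrated effect over the sham arm it randomises. Non-inferiority could therefore be concluded from two ineffective treatments.

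For margins from 0.35 to 0.7 SD, the illustrative chance of this is about 19% to 45% with 10 per arm and 21% to 51% with 12, against about 2% with the sham condition. These figures rest on an assumed margin, a one-sided 0.05 test, equal variances and no true effect in any arm. The logical gap does not depend on which margin is chosen. It should be corrected before analysis.

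**What to change.** Reconcile the Introduction, Sample Size Estimation and Statistical Analysis as follows.

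1. Make real rTMS versus sham on the STT the first test: superiority, two-sided 0.05. This carries out the Introduction's hypothesis.
2. If the non-inferiority aim is kept, state and justify a margin, and test rTMS against training only if step 1 succeeds.
3. Report training versus sham with its 95% confidence interval in all cases.
4. If neither rTMS nor training beats sham, do not report the comparison with training as non-inferiority. If only training beats sham, report the rTMS versus training interval descriptively.

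The change needs a few sentences and no new data. A fixed sequence needs no split of alpha between the two tests.

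The cost is in power and should be stated openly. At d = 0.7 with 10 to 12 per arm, step 1 has about 32–38% power, and the full sequence at a 0.7 SD margin succeeds in about 23–28% of trials. The stated 90% power must therefore be restated for the comparisons actually made. Either the trial is enlarged (about 43 per group for step 1 alone at 90%) or the limited power is acknowledged.

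### The planning effect size of 0.7 comes from training effects in MCI, so the stated power of 0.9 does not describe rTMS versus training or rTMS versus sham

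*Protocol article*

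**What the plan says.** Protocol article, Sample Size Estimation, names the framework first, with the training arm as the reference: "Sample size calculations were based on non-inferiority tests, as the purpose of this study was to show that the rTMS intervention was not inferior to". The only empirical inputs follow: "According to studies showing that the effect size of working memory training on MCI is 0.74 and executive function is 0.575". The settings entered into the software are "effect size is 0.7, α is 0.05, power is 0.9". Samples of 10, 10 and 10 "are obtained for the three groups". For attrition, "two additional patients will be added to each group to compensate for possible dropouts", and so "A total of 12 patients will be allocated to each group".

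The hypothesis in the Introduction is a different one, namely that four weeks of bilateral rTMS "is more effective in improving cognitive function in patients with TBI than sham stimulation and cognitive training". Statistical Analysis plans ANOVA across the three groups with Bonferroni-corrected post hoc comparisons. Under Inclusion Criteria the patients have a TBI at least 6 months old. The Introduction mentions two randomised trials of rTMS in TBI. One of them "Reported That Stimulating the Left DLPFC With 10 Hz RTMS Did not Improve Cognitive Function in Subjects", and the other is described as positive. Neither enters the sample size section.

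**The concern.** Two comparisons matter here: rTMS with training, and rTMS with sham. Power for the first needs either a non-inferiority margin together with an assumed true difference, or an assumed superiority difference. Power for the second needs an assumed rTMS-minus-sham difference. The section supplies none of these. Its two figures describe what training, the comparator, achieves in a different patient group, and neither is a difference between rTMS and anything.

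The stake is how the result will be read. If rTMS and training do not differ significantly, or non-inferiority is not shown, a reader will take the result as coming from a trial with 90% power for that question. If the real power is well under one half, such a result says little either way. The same holds for rTMS versus sham.

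**Working it through.** **Inputs.** From Sample Size Estimation: effect size 0.7 (metric not stated), α = 0.05 (sidedness not stated), power 0.9, three groups, n = 10 per group before and 12 after the dropout allowance. From Statistical Analysis: Bonferroni post hoc tests, taken here as three pairs, so α = 0.05/3 = 0.0167.

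**Step 1. Reproduce the plan's figure.** Take a three-group one-way ANOVA with 0.7 as Cohen's f. The noncentrality is λ = N·f².
- n = 10 per group: λ = 30 × 0.49 = 14.7, df 2 and 27, critical F = 3.354, power = 0.911.
- n = 9 per group: λ = 27 × 0.49 = 13.23, power = 0.873.

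So 10 is the smallest n per group that reaches 0.9, and the plan's figure is recovered. This test asks whether any of the three means differ. It is neither a non-inferiority test nor a contrast of rTMS with one comparator. An f of 0.7 also implies that the extreme groups lie 0.7 × 3/√2 = 1.48 SD apart (one group differs) to 0.7 × √6 = 1.71 SD apart (evenly spaced).

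**Step 2. The test the section names.** Read 0.7 as a non-inferiority margin in SD units, with true difference 0. For two arms of n, the noncentrality is δ = 0.7·√(n/2), with df = 2n − 2.
- n = 10: δ = 0.7 × √5 = 1.565. Power is 0.445 at one-sided 0.05 and 0.316 at one-sided 0.025.
- n = 12: δ = 1.715. Power is 0.507 and 0.374.
- Power 0.9 would need 35 (one-sided 0.05) or 43 (one-sided 0.025) per group by the normal approximation.

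**Step 3. The hypothesis in the Introduction.** Read 0.7 as a pairwise standardised difference for superiority; δ is as in Step 2.
- n = 10: power is 0.317 at two-sided 0.05 and 0.171 with Bonferroni for three pairs.
- n = 12: power is 0.375 and 0.215.

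**Step 4. A smaller rTMS-minus-training difference.** The documents give no such difference. As an illustration only, assume that rTMS achieves 1.0 SD and training 0.74 or 0.575 SD on the same scale. The difference is then 1.0 − 0.74 = 0.26 or 1.0 − 0.575 = 0.425 SD. Superiority power at two-sided 0.05 is:

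| n per arm | 0.26 SD | 0.425 SD |
|---|---|---|
| 10 | 8.5% | 14.7% |
| 12 | 9.4% | 16.9% |

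**Step 5. What 10 per arm can detect.** Power of 0.9 for one pair needs a difference of about 1.36 SD (one-sided 0.05) or 1.53 SD (two-sided 0.05).

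**The case against.** The best defence is that the section names non-inferiority. In that framework the comparator's own effect is a legitimate input, because it informs the margin, and equal effects of rTMS and training are the usual planning assumption. This stands, and it limits the point. A reader might infer that using a training effect at all is the error, or that power collapses to 5% if rTMS merely equals training. The documents do not support either inference. The 5% is the type I error of a superiority test, and under non-inferiority with equal effects the power depends on the margin. Likewise, 8.5% to 15% applies only to the superiority hypothesis. With 0.7 as the margin and a true rTMS advantage of 0.26 or 0.425 SD, non-inferiority power at 10 per arm is about 66% or 78% (one-sided 0.05). That is much higher, though still below 0.9. The defence does not rescue the section, however: it calls 0.7 an effect size and states no margin. A margin of 0.7 would also exceed the whole cited executive-function effect of 0.575, if the two are on the same scale.

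A second defence is that 0.9 does match a planned analysis, since the ANOVA compares all three groups. That is true of the omnibus F test in Step 1, so it would be too strong to say that the stated power belongs to no test in the trial. But it is not the test on which the section says it relies, and a significant F does not show how rTMS compares with training or sham.

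A third is that direct evidence is scarce: two conflicting TBI trials, described without effect sizes, each stimulating one side, whereas this trial stimulates both. Borrowing from another cognitively impaired population is common in that position. This is fair, and the borrowing is better called unjustified than absurd. It still has to be labelled, and a value for the right contrast has to be given.

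It is also tempting to add 0.7 to the cited figures and say how large the rTMS effect over no treatment would have to be. The section gives neither the metric nor the control condition behind 0.74 and 0.575, so such a sum is not supported.

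Finally, a non-inferiority calculation can reach 10 per arm if one adds, for example, a margin of 0.7 and a true rTMS advantage of 0.7 (exact t, one-sided 0.05). Nothing in the section states that.

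**Conclusion.** The point holds in this form: the planning value comes from training in MCI, no rTMS contrast or margin is specified, and the stated 0.9 does not describe rTMS versus training or rTMS versus sham. If 0.7 is taken at face value for those contrasts, power at 10 per arm is 17% to 44%, depending on the framework, sidedness and Bonferroni correction. At 12 per arm it is about 21% to 51%. These figures assume a two-group comparison in SD units without baseline adjustment, and a true difference of 0 for non-inferiority. With adjustment at an assumed baseline correlation of 0.5 to 0.8, a 0.7 difference would still need 14 to 27 per group one-sided, or 17 to 34 two-sided, for power 0.9. The 8.5% to 15% range rests on an assumed rTMS advantage of 0.26 to 0.425 SD over training and applies to superiority only.

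This should be corrected before results are read. It misstates what the trial can show, but does not invalidate its conduct.

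**What to change.** Rewrite the Sample Size Estimation paragraph as follows.

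- Label 0.74 and 0.575 as effects of training in MCI, and stop using them as the planning difference.
- Reconcile the non-inferiority purpose stated there with the superiority hypothesis in the Introduction, and say which applies to rTMS versus training.
- For rTMS versus training, state either a non-inferiority margin on the Shape Trail Test (with its justification and the assumed true difference) or an assumed superiority difference. For rTMS versus sham, state an assumed difference. Source each from TBI, or label it as an assumption and give a range.
- State the effect-size metric and the sidedness of α.
- Restate power for each contrast at the fixed 10 to 12 per arm. Where it is low, say that the contrast will be reported as an estimate with its confidence interval.

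The cost is one reworded paragraph and a less favourable stated power. The number of patients, visits and assessments does not change.
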